# PLAN-psoriasis: protocol for a randomised controlled feasibility trial comparing patient-led ‘as-needed’ treatment and therapeutic drug monitoring-guided treatment to continuous treatment for adults with clear or almost clear skin on risankizumab monotherapy for psoriasis

**DOI:** 10.1136/bmjopen-2025-106635

**Published:** 2025-10-10

**Keywords:** Clinical Protocols, DERMATOLOGY, Psoriasis, Drug Therapy

## Abstract

**Introduction:**

Targeted biologic therapies have transformed outcomes for individuals with psoriasis, a common immune-mediated inflammatory skin disease. The widespread use of these highly effective treatments has led to a growing number of individuals with clear or nearly clear skin remaining on continuous, long-term treatment. Personalised strategies to minimise drug exposure may sustain long-term disease control while reducing treatment burden, associated risks and healthcare costs. This study aims to evaluate the feasibility of a definitive pragmatic effectiveness trial of two personalised dose minimisation strategies compared with continuous treatment (standard care) in adults with well-controlled psoriasis receiving the exemplar biologic risankizumab.

**Methods and analysis:**

This is a multicentre, assessor-blind, parallel group, open-label randomised controlled feasibility trial in the UK, evaluating two personalised biologic dose minimisation strategies for psoriasis. 90 adults with both physician-assessed and patient-assessed clear or nearly clear skin on risankizumab monotherapy for ≥12 months will be randomised in a 1:1:1 ratio to (1) patient-led ‘as-needed’ treatment, where risankizumab is administered at the first sign of self-assessed psoriasis recurrence, (2) therapeutic drug monitoring-guided treatment, with personalised dosing intervals determined using a pharmacokinetic model or (3) continuous treatment as per standard care, for 12 months. Participants will be invited to submit self-reported outcomes and self-taken photographs every 3 months using a bespoke remote monitoring system (mySkin app) and will attend an in-person assessment at 12 months. They may also request additional patient-initiated follow-up appointments during the trial if needed. The primary outcome is the practicality and acceptability of the two personalised biologic dose minimisation strategies, assessed as a composite measure including recruitment and retention rates, adherence to the assigned strategies and acceptability to both patients and clinicians. The feasibility of collecting healthcare cost and resource utilisation data will also be evaluated to inform a future cost-effectiveness analysis. A nested qualitative study, involving semistructured interviews with patients and clinicians, will explore perspectives on the personalised biologic dose minimisation strategies. These findings will inform the design of a future definitive trial.

**Ethics and dissemination:**

This study received ethical approval from the Seasonal Research Ethics Committee (reference 24/LO/0089). Results will be disseminated through scientific conferences, peer-reviewed publications and patient/public engagement events. Lay summaries and infographics will be codeveloped with patient partners to ensure the findings are accessible for the wider public.

**Trial registration number:**

ISRCTN17922845.

STRENGTHS AND LIMITATIONS OF THIS STUDYThe study will provide data on the feasibility of personalised biologic dose minimisation strategies in well-controlled psoriasis.Participants will be recruited from multiple dermatology departments in the UK, including both academic and non-academic centres.This study leverages novel digital platforms to streamline trial processes and reduce the need for in-person visits.The design and delivery of the study has been informed by extensive patient and public involvement.The study is not powered to evaluate clinical effectiveness.

## Introduction

### Background and rationale

 Chronic plaque psoriasis is a common immune-mediated inflammatory disease affecting over 125 million people worldwide.^1^ It is characterised by red, scaly skin plaques and is associated with multiple comorbidities including depression, cardiometabolic syndrome and psoriatic arthritis.^2^ Although there is currently no cure, advances in the understanding of psoriasis pathophysiology have led to the development of biologic therapies targeting key inflammatory pathways involved in disease progression, including tumour necrosis factor (TNF), interleukin-17 (IL-17) and interleukin-23 (IL-23).^2^ Biologic therapies have transformed outcomes for individuals with psoriasis, with up to 60% achieving complete skin clearance at 12 months.^3^,^5^

The widespread adoption of biologic therapies in routine care has resulted in a growing population of individuals with well-controlled psoriasis receiving continuous, long-term treatment. Although highly effective, biologic therapies are associated with dose-dependent adverse events, including increased susceptibility to infections and, more rarely, serious complications such as demyelination.^6^,^9^ These risks remain a concern for patients: during the COVID-19 pandemic, a global cross-sectional survey found that one in four patients discontinued biologic treatment, with nearly half citing concerns over long-term immune suppression.^10^ The high cost of biologic treatment and the burden associated with ongoing injections and hospital visits further highlight the need for optimised treatment strategies that reduce drug exposure while sustaining disease control. Although recent surveys indicate support among dermatologists for biologic dose minimisation in patients with well-controlled psoriasis, real-world implementation remains variable due to limited robust, high-quality evidence to guide safe and effective dose reduction without increasing the risk of disease flares.^11 12^

Emerging evidence indicates that durable disease control may be achievable through strategies that reduce biologic exposure. Several studies have shown that disease control can often be maintained for extended periods following biologic discontinuation and is typically regained quickly on retreatment, without major safety concerns.^413^,^17^ A recent systematic review reported median times to relapse ranging from 12 to 34 weeks following biologic discontinuation, with longer periods of disease control observed after cessation of IL-23 inhibitors.^18^ Notably, in most studies, biologic discontinuation occurred relatively early in the treatment course (typically between 12 and 28 weeks), shortly after disease control was achieved.^1315^,^17^ This raises the possibility that maintaining disease control for a longer duration prior to discontinuation may lead to even more favourable outcomes.

To date, most biologic dose minimisation studies in psoriasis have employed standardised, stepwise dose reduction protocols, applying the same tapering schedule across all participants.^19 20^ While structured, this ‘one-size-fits-all’ approach does not account for individual variation. As healthcare models seek to become increasingly personalised, there is a need for more flexible, individualised strategies. One such approach involves adjusting the biologic dosing interval based on individual response, so further doses are only given if disease control is no longer maintained.^21^ As self-reported skin status is a reliable method for monitoring psoriasis,^22^ patients are well positioned to detect disease recurrence themselves through the appearance of a skin plaque. This opens the possibility of a patient-led ‘as-needed’ approach, in which biologic treatment is paused and restarted by the patient at the first sign of recurrence.^23^ This strategy may enhance patient empowerment and reduce treatment burden; however, its safety and effectiveness in real-world clinical settings remain untested.

Another personalised approach involves using serum drug levels to guide dosing. Pharmacokinetic (PK) data across multiple classes of biologics including IL-23, IL-17 and TNF inhibitors indicate that in individuals who are established on treatment, serum drug concentrations often exceed the levels required for disease control.^24^,^26^ An exposure–response analysis of the exemplar IL-23 inhibitor biologic risankizumab in phase II and phase III trials found that average serum drug concentration, rather than trough level, was the stronger predictor of treatment response.^26^ Patients with higher average serum risankizumab concentrations were more likely to achieve disease control, suggesting that serum drug level-guided dose adjustments may allow individualised dose reductions without compromising efficacy.^26^ We have developed a model-informed precision dosing approach using Bayesian estimation to predict individual PK parameters to generate personalised dosing intervals for risankizumab (via a user-friendly online dashboard).^27^ However, the acceptability of implementing therapeutic drug monitoring (TDM)-guided biologic dosing in routine psoriasis care, and the feasibility of delivering a definitive pragmatic effectiveness trial, remains to be established.

### Objectives

The primary objective of this study is to determine the practicality and acceptability, to both patients and clinicians, of two personalised biologic dose minimisation strategies compared with continuous treatment in adults with chronic plaque psoriasis who have been clear or nearly clear for ≥12 months on risankizumab monotherapy. The treatment strategies are:

Patient-led ‘as-needed’ treatment: risankizumab is self-administered at the first self-assessed sign of psoriasis recurrence, supporting patient empowerment and self-management.^23^TDM-guided treatment: a PK model-informed precision dosing approach is used to generate a personalised dosing interval (via an online dashboard), based on serum risankizumab concentration and individual covariates.^27^Continuous treatment: ongoing fixed interval risankizumab dosing, as per standard care.

The secondary objectives are to:

Provide preliminary data on the potential clinical effectiveness, safety, tolerability and treatment burden of (1) patient-led ‘as-needed’ treatment and (2) TDM-guided treatment compared with (3) standard care (continuous treatment). These data will allow estimation of effect sizes to inform sample size calculations for a future definitive trial.Assess the feasibility of collecting data on healthcare costs and resource use for each treatment strategy.Refine the model-informed precision dosing dashboard for TDM-guided risankizumab dosing using longitudinal PK data and pharmacodynamic (PD) data, to enhance its future utility.^27^

The exploratory objectives are to:

Determine the feasibility of self-sampling blood, which may be used in future research and clinical care.Determine the feasibility of genotype testing, which may be used in future research and clinical care.

## Methods and analysis

### Study design and setting

Patient Led As Needed (PLAN)-psoriasis is a multicentre, assessor-blind, parallel group, open-label, feasibility randomised controlled trial (RCT) with economic scoping and a nested qualitative study (figure 1). It will be conducted across multiple hospital dermatology departments in the UK, representing a mix of academic and non-academic centres (online supplemental table 1).

**Figure 1 F1:**
[figure not shown]
Trial design. PIFU, patient-initiated follow-up; TDM, therapeutic drug monitoring.

### Participants and recruitment

Participants are eligible for the trial if they meet the inclusion and exclusion criteria outlined in table 1. Figure 2 summarises the flow of participants through the study.

**Table 1 T1:** Eligibility criteria

Inclusion criteria	Exclusion criteria
Adults aged ≥16 years with a diagnosis of chronic plaque psoriasis with evidence of clear or nearly clear skin on risankizumab monotherapy for ≥12 months. Physician Global Assessment of clear or nearly clear skin at study entry. Clinician assessed Psoriasis Area and Severity Index ≤2 at study entry. Patient Global Assessment of clear or nearly clear skin at study entry.	Receiving risankizumab for a primary indication other than psoriasis. Concomitant immune-modifying therapy or phototherapy.

**Figure 2 F2:**
[figure not shown]
Participant flow chart. PASI, Psoriasis Area and Severity Index; PGA, Physician Global Assessment; PIFU, patient-initiated follow-up; TDM, therapeutic drug monitoring.

Potentially eligible participants will be identified by the clinical team at each study site during routine clinical care visits, as well as from individuals scheduled to attend the sites. Additionally, relevant research databases will be searched, and individuals with psoriasis who have consented to be contacted about related research studies will be approached. To maximise reach, study details will also be disseminated through national and regional networks, including the UK Dermatology Clinical Trials Network, the Psoriasis Association, relevant websites, newsletters and social media channels. In line with the National Institute for Health and Care Research’s (NIHR’s) Research Inclusion Strategy, efforts will be made to engage with individuals from diverse backgrounds to ensure the study population is representative of the wider psoriasis population.^28^
^29^ To further promote inclusivity, individuals will also have an opportunity to self-refer into the study.

All individuals who express interest will have the opportunity to discuss the study with a member of the research team and will be provided with an information sheet. They will be given sufficient time to consider their participation. Written informed consent will be obtained electronically (eConsent) from each participant prior to study enrolment by a member of the research team. Table 2 outlines the study procedures in the trial.

**Table 2 T2:** Study procedures for Patient Led As Needed (PLAN)-psoriasis

	Screening	Baseline		Month 3	Month 6	Month 9	Month 12	PIFU
		Baseline and randomisation	Training					
Informed consent	X							
Eligibility	X	X						
Demographics	X							
Medical history	X	X	X	X	X	X	X	X
Blood sample*	X				†		X	X
Randomisation		X						
Education‡			X					
Clinical assessments (in-person)								
PASI	X	§					§	X
Physician Global Assessment	X	§					§	X
Body mass index		X						
Waist circumference		X						
Patient reported outcome measures								
Patient Global Assessment	X	X		X	X	X	X	X
DLQI			X	X	X	X	X	X
EQ-5D-5L			X	X	X	X	X	X
Itch NRS			X	X	X	X	X	X
PHQ			X	X	X	X	X	X
GAD			X	X	X	X	X	X
BIPQ			X	X	X	X	X	X
PsAID			X	X	X	X	X	X
PEST			X	X	X	X	X	X
Injection log			X	X	X	X	X	X
Photographs			X	X	X	X	X	X
Adverse events recording				X	X	X	X	X
Adherence and acceptability questionnaires					X		X	
Resource use			X	X	X	X	X	X
Nested qualitative study								
Semistructured interviews¶							X	

* Serum albumin, creatinine, C reactive protein, risankizumab concentration, anti-risankizumab antibody titre.

† Self-taken blood sample.

‡ Training provided on treatment strategy, PIFU and the mySkin app.

§ Assessor-blind skin assessments.

¶ Subset of participants and clinicians only.

BIPQ, Brief Illness Perception Questionnaire; DLQI, Dermatology Life Quality Index; EQ-5D-5L, EuroQol 5-Dimension 5-Level; GAD, Generalised Anxiety Disorder Questionnaire; NRS, Numerical Rating Scale; PASI, Psoriasis Area and Severity Index; PEST, Psoriasis Epidemiology Screening Tool; PHQ, Patient Health Questionnaire; PIFU, Patient-Initiated Follow-Up; PsAID, Psoriatic Arthritis Impact of Disease.

### Randomisation and blinding

Participants will be randomised (1:1:1 ratio) to one of three treatment strategies: (1) patient-led ‘as-needed’ treatment, (2) TDM-guided treatment and (3) continuous treatment (standard care). Randomisation will be conducted via a secure online system to ensure allocation concealment. Stratification will be based on recruiting site and clear or nearly clear skin status, with randomly varying block sizes used to maintain allocation concealment and achieve balanced group sizes across these categories.

Although participants and the research team will not be blinded to the treatment strategy allocated, disease severity assessments, including the Psoriasis Area and Severity Index (PASI) and Physician Global Assessment, will be conducted by an assessor who is blinded to treatment allocation and is not involved in the participant’s care. Participants will be asked not to reveal their allocated treatment strategy to this blinded assessor. The blinded assessor will be either a dermatologist or a dermatology nurse.

### Interventions

Following randomisation, all participants will receive training on their assigned treatment strategy, which they will follow for the 12-month study period. Topical treatments can be used as usual across all treatment strategies. Routine follow-up is scheduled at month 12 (study end), after which participants will return to National Health Service (NHS) care. Participants may continue with their assigned treatment strategy beyond the study period if they wish, following discussion with their clinical team.

Participants will be invited to use the mySkin app to submit self-reported outcomes and self-taken photographs at three-monthly intervals throughout the 12-month study period. Disease severity at each timepoint will be assessed using the self-reported Patient Global Assessment. This approach is supported by prior research demonstrating concordance between patient and clinician-assessed disease severity in psoriasis, especially at low disease activity.^30^ No routine in-person follow-up visits are scheduled prior to the final follow-up at month 12.

The mySkin app is designed to streamline trial procedures, promote patient empowerment and minimise unnecessary clinic visits. It enables remote collection of patient-reported outcomes and self-taken photographs (including step-by-step guidance to optimise/standardise photograph capture). The app also includes an injection log to record administered biologic injections and displays each participant’s assigned treatment strategy, along with a personalised dashboard showing when their next biologic dose is due.

The mySkin app provides step-by-step instructions for self-sampling of blood for serum analysis (aligned with a supporting video, https://bit.ly/taking-blood-sample). All participants will be invited to collect up to 1 mL of blood using serum microtubes at month 6. Self-sampling kits will be mailed to participants’ homes in advance, and they will be asked to return their samples to the central study team using prepaid packaging. Participants will also be invited to complete an in-app questionnaire to assess the acceptability of self-sampling of blood, incorporating relevant constructs from the theoretical framework of acceptability.^31^

Throughout the study, participants may request ad hoc patient-initiated follow-up (PIFU) visits via the mySkin app if they rate their psoriasis severity as moderate or worse based on the Patient Global Assessment, or if they have concerns about any intercurrent issues. PIFU visits will occur within 5 working days of participant request.

For participants unable to use the mySkin app, the research team will arrange alternative methods of data collection such as paper forms. Participants without access to a smartphone will be provided with an electronic device and the necessary training. All participants may also access further support from the research team via telephone if needed.

#### Intervention arm 1: patient-led ‘as-needed’ treatment

Participants randomised to patient-led ‘as-needed’ treatment will pause risankizumab monotherapy and resume it at the first sign of self-assessed psoriasis recurrence to maintain clear or nearly clear skin, keeping a minimum dosing interval of 12 weeks^23^. Recurrence is defined as Patient Global Assessment Score of mild (ie, no longer clear/nearly clear).

#### Intervention arm 2: TDM-guided treatment

For participants randomised to TDM-guided treatment, a clinician will use an online precision dosing dashboard incorporating a PK model for risankizumab therapy to calculate a personalised dosing interval, which will be applied throughout the 12-month study period.^27^ To generate this interval, the dashboard requires the serum concentration of risankizumab and the anti-risankizumab antibody titre, measured using routine rapid chemiluminescence assays following the screening visit. The dashboard also requires the date of the last risankizumab dose, body weight, PASI and the serum levels of albumin, creatinine and C reactive protein.

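### Body weight is a required dashboard input but is scheduled only at baseline, so the later drug-level samples used to refine the dosing model have no concurrent weight

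*Protocol article*

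**What the plan says.** The section on intervention arm 2 (TDM-guided treatment) states that "the dashboard requires the serum concentration of risankizumab and the anti-risankizumab antibody titre". It adds the date of the last dose and "body weight, PASI and the serum levels of albumin, creatinine and C reactive protein". That makes eight inputs in all.

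Table 2 (study procedures) shows when each can be collected. The footnote to the blood sample row gives its content as "Serum albumin, creatinine, C reactive protein, risankizumab concentration, anti-risankizumab antibody titre", and the row is marked at screening, month 6 (self-taken), month 12 and PIFU. PASI is listed under in-person clinical assessments and is marked at screening, baseline, month 12 and PIFU. For dose dates, the Interventions section says that "The app also includes an injection log to record administered biologic injections", and Table 2 marks this log at training, every three-monthly point and PIFU. There is no row for body weight. "Body mass index" is marked once, at the baseline and randomisation visit, as is "Waist circumference".

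The Objectives section includes, as a secondary objective, to "Refine the model-informed precision dosing dashboard for TDM-guided risankizumab dosing using longitudinal PK data and pharmacodynamic (PD) data". The list of secondary outcomes repeats this.

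**The concern.** The new information for the refinement is the set of drug levels taken after baseline, at month 6, month 12 and PIFU visits. The authors' own model needs weight to interpret a drug level, yet the latest scheduled weight may be up to 12 months old when the level is drawn. If weight acts on clearance, a participant whose weight has changed will have a drug level that has shifted for a known reason, but the data set will not contain that reason. A model holding the baseline weight would have to place the shift in clearance, in another covariate or in residual error.

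What is at stake is the quality of the data for one secondary objective. A weight that was never taken cannot be supplied later by an analysis plan, so this is a matter for the visit schedule.

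**Working it through.** The plan gives no figure on this point to reproduce. The check has two parts: inputs against schedule, then the possible size.

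**1. Inputs against schedule.** Inputs are from the TDM-guided treatment section; timings are from Table 2 and its footnotes.

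| Dashboard input | Source in Table 2 | Month 6 | Month 12 | PIFU |
|---|---|---|---|---|
| Risankizumab concentration | Blood sample | self-taken | yes | yes |
| Antibody titre | Blood sample | self-taken | yes | yes |
| Albumin | Blood sample | self-taken | yes | yes |
| Creatinine | Blood sample | self-taken | yes | yes |
| C reactive protein | Blood sample | self-taken | yes | yes |
| Date of last dose | Injection log | yes | yes | yes |
| PASI | PASI | no | yes | yes |
| Body weight | Body mass index (inferred) | no | no | no |

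Seven of the eight inputs recur at both month 12 and PIFU; weight recurs at neither. At month 6 both weight and PASI are absent. The medical history row recurs at every visit, but nothing says that it records weight. That weight is taken even at baseline is an inference from the body mass index row.

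**2. Size for one person.** The documents do not say how weight enters the model. Assume clearance is proportional to weight raised to the power θ, with weight held at its baseline value. For a fractional weight change d, the misattributed change in clearance is (1 + d)^θ − 1. Both θ and d are assumptions.

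- d = +5%: θ = 0.75 gives 1.05^0.75 − 1 = 3.7%; θ = 1.0 gives 5.0%.
- d = +10%: θ = 0.75 gives 1.10^0.75 − 1 = 7.4%; θ = 1.0 gives 10.0%.
- Wider range, θ = 0.5 to 1.25: 2.5% to 6.3% for d = +5%, and 4.9% to 12.7% for d = +10%.
- θ = 0: no effect.

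**3. Size for the population.** If weight changes average zero with SD s, the spurious variation in clearance has SD of about θ × s on the log scale. Combined with a between-person SD b, the total is √(b² + (θs)²). With assumed s = 3% to 8%, θ = 0.5 to 1.25 and b = 20% or 30%:

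- smallest: θs = 0.5 × 0.03 = 0.015, so 20% becomes 20.1% and 30% stays at 30.0%;
- largest: θs = 1.25 × 0.08 = 0.10, so 20% becomes √(0.04 + 0.01) = 22.4% and 30% becomes √(0.09 + 0.01) = 31.6%.

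This compares spurious variation with between-person spread. It does not measure the effect on within-person change over time, which longitudinal data are meant to inform.

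If weight change is systematic, it does not average out. A mean gain of 2% would appear as a mean clearance change of 1.5% (θ = 0.75) to 2.0% (θ = 1.0).

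**The case against.** The strongest reply is that the documents do not show the model. They do not say that weight acts on clearance, nor that the refinement would carry the baseline weight forward. This stands, and it makes the consequence conditional. A reader might infer that the refinement will necessarily read weight change as changed clearance; the text does not support that.

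A second reply is that the dashboard inputs are listed for setting the trial interval. That interval is calculated once, from measurements taken around screening and baseline, and is kept for the whole 12 months. This also stands. A reader might turn the clearance percentages into weeks of dosing interval, but no participant's allocated interval moves because of a missing later weight. In later use the dashboard would ask for a weight at that time. Nor do the documents plan to re-run the dashboard at month 12, so the lack of a complete current input set at that visit is not in itself a failure of the plan.

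A third reply is that an article condenses the full protocol, and that covariate handling belongs in a PK analysis plan. This holds for how weight is modelled. It does not hold for when weight is measured: Table 2 is an explicit visit-by-visit schedule that marks body mass index at one visit and leaves the others blank.

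Finally, zero-mean weight changes add little to the between-person spread. This is fair and limits the importance of the point, subject to the caveat about within-person change.

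**Conclusion.** The mismatch between Table 2 and the refinement objective is real but minor. The PK samples taken after baseline have no scheduled concurrent weight, although weight is a required input and the other seven inputs are collected again at month 12 and PIFU. If weight affects clearance and baseline weight is carried forward, a 5% to 10% weight gain corresponds to about 4% to 10% in that person's predicted clearance, with assumed exponents of 0.75 to 1.0. The effect on population parameters is probably small unless participants' weights drift in one direction. The exponents, weight changes and between-person SDs are all assumptions. The primary feasibility outcome and dosing within the trial are not affected.

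**What to change.** In Table 2, mark body weight at month 12 and at PIFU. Add one self-reported weight question in the app beside the month 6 self-taken sample. Use the weight concurrent with each sample when refining the model.

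The cost is one weighing at visits where PASI is already scored in person and blood already taken, one app question, and a minor amendment to the schedule. Self-reported weight at month 6 will be less accurate than a measured one.

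Timing matters. The first participant was randomised in December 2024 and follow-up is expected to end by July 2026, so weights are lost as month 12 visits pass. Where no later weight exists, state that the baseline value is carried forward and examine the effect in a sensitivity analysis.
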